**Fig. 2 Fig2:**
[figure not shown]
Schedule of enrolment, interventions, and assessments

### Settings and study participants

Prospective participants will be recruited from 38 aged care facilities in urban and rural Victoria, Australia. Before enrolment or study assessments being performed, prospective participants will be asked to sign a written consent form. Residential care staff will identify participants who are cognitively able to give informed consent. Participants who consent to participate in the study will be screened for study eligibility by a research assistant.

The inclusion criteria are:Presenting distance < 6/12 (0.30; Logarithm of the Minimum Angle of Resolution-LogMAR) and/or near vision ≤ N8 (1.00 M) assessed uniocularly and binocularly using the Bailey-Lovie LogMAR [16] charts;Able to speak English;Moderate cognitive functioning or better as assessed by the Psychogeriatric Assessment Scale (PAS) [17] (score ≤ 15);Ability to undergo VA testing and provide reliable results.

The exclusion criteria are:Residents in respite care (short-term stay);Severe cognitive impairment (score of ≥ 16 on the PAS);Non-English speaking;Inability to be tested for vision;Contraindication(s) as indicated by the general practitioner responsible for the resident’s care.

### Randomization

An independent statistician will perform the randomization sequence generation using a computer-generated list. For logistical reasons and to minimize confounding effects, stratified cluster randomization designs will be used to randomize participants by residential aged care facility (stratified by size and region) to the intervention (ROC) or control (usual care) arm. Participants in the same aged care facility will all be assigned to the same study arm. The allocation sequence will be concealed from the research assistants enrolling and assessing participants. Residential care facility staff, the research study coordinator, and the eye health professionals delivering ROC will not be masked to the group allocation as this is impractical.

### Participant flow

All prospective participants who sign a study consent form will undergo a screening examination. When inclusion and exclusion criteria are met, the participant will be invited to complete a pre-intervention face-to-face baseline assessment with a research assistant. Following the baseline assessment, participants will receive the ROC intervention or usual care. All participants will be invited to complete follow-up assessments at two and six months after baseline visits.

### Intervention

The ROC model of eye care includes an on-site eye examination by an optometrist with expertise in domiciliary and low vision care. Four intervention options will be provided to help improve vision based on the individual participants’ eye history. These include: (1) refraction and spectacle provision; (2) cataract surgery; (3) referral to an ophthalmologist for medical and surgical treatments for conditions likely to cause loss of sight or ocular discomfort; and (4) low vision rehabilitation for untreatable eye disease. If a clinical need is identified, participants will be eligible to receive more than one intervention pathway (e.g. spectacles and low vision rehabilitation aids/services). For all pathways, transportation costs for initial consultations and for up to two follow-up consultations (to either a public or private care provider) will be funded by the study.

#### Refractive correction

An optometrist from the ACO will perform a detailed refraction for distance and near vision and measure best corrected VAs. Participants will be allocated to the refractive correction pathway if they meet the following criteria:Presenting VA < 6/12 (0.3 LogMAR) for distance or N8 (1.00 M) or worse for near which is improved by refractive correction by at least two lines/10 letters on a LogMAR Chart and/or 0.2 Log units for near in at least one eye;Participant has no other ocular co-morbidities requiring referral or urgent treatment that would affect the outcome of the refractive assessment and prescription of glasses.

If participants meet the above criteria, they will be prescribed, dispensed, and supplied with the appropriate spectacles from a selected range according to their visual needs and activities. One pair of spectacles (or two if separate distance and reading glasses are needed) will be provided and dispensed by the ACO and funded by the study.

#### Cataract surgery

The ACO optometrist will determine whether a participant will be referred for cataract surgery assessment by an ophthalmologist following the grading of lens opacities using the grading World Health Organization (WHO) Simplified Cataract Grading System [18]. Participants will be allocated to the cataract surgery pathway if they meet the following criteria:VA < 6/12 (0.3 LogMAR) that is not corrected by refractive correction by > 2 lines/10 letters;Phakic in at least one eye (can be pseudophakic in one eye);Evidence of lens opacities on anterior segment examination;No other ocular conditions identified by fundus or self-report requiring referral or urgent treatment before cataract surgery.

If spectacles are required following cataract surgery, these will be dispensed by ACO and funded by the study.

#### Referral to an ophthalmologist

A referral to an ophthalmologist will be provided if the participant has unexplained poor VA (< 6/12; 0.3 LogMAR) that is not due to uncorrected refractive error or cataract or shows evidence of AMD, DR, and/or glaucoma, and are not currently receiving ophthalmic advice/treatment for these conditions. Following medical consultation with a resident, treatment options, both surgical and medical, may be offered through the public health system, at the discretion of the treating ophthalmologist. Treatment options could include intraocular injections for conditions such as wet AMD and DR, surgical interventions for advanced glaucoma (i.e. trabeculoplasty), and the provision of topical medication for glaucoma, ocular inflammation, lid disease, and ocular infection. Other retinal eye conditions that require referral include (but are not limited to): retinal vein occlusion or emboli; macular hole; retinal detachments; retinal collaterals; and naevus. The study coordinator will liaise with the residential facility in organizing the initial ophthalmologist appointment and two subsequent follow-up appointments as required.

#### Low vision rehabilitation

Participants with VA < 6/12 (0.3 LogMAR) not correctable by either refraction or cataract surgery will be eligible for the low vision rehabilitation pathway. An ACO optometrist will undertake an initial comprehensive vision and ophthalmic review and provide low vision aids where appropriate at no cost. The type of low vision aids provided will be determined by the level of VI, the level of magnification required to perform desired tasks and the participant’s ability to use aids of different designs. Detailed demonstration, training, and instruction on aids will be given to the participant. Details of this examination will be forwarded with referral to the nearest Vision Australia center, Australia’s leading provider of blindness and low vision rehabilitation services, where an appointment will be scheduled within eight weeks. At this appointment, a Vision Australia Occupational Therapist will conduct a “Techniques for Daily Living” session with the participant, focusing on areas of difficulty and concern. Each session will be adapted to the individual circumstances of the resident, but be based around application of the following techniques:*Lighting:* general and/or task lighting;*Size:* bring things closer, make them larger, and vary the use of prescribed magnification;*Contrast:* increase the contrast between the foreground and the background;*Senses:* touch, scent, sound, and taste;*Marking:* tactile and/or contrast colored marking;*Labeling:* large print, Braille, or audio labels;*Organization:* different systems for organizing belongings;*Equipment:* everyday devices and/or functional use of low vision aids.

### Usual care

Residents with VI in the usual care group will be referred for an evaluation to the eye care service associated with the facility or a practitioner of their choice.

### Outcomes

#### Distance and near vision (primary)

Distance presenting VA at the two- and six-month follow-up visits after baseline. Participants’ uniocular and binocular distance VA (LogMAR charts) will be assessed, according to established protocols with their current presenting correction.

Uniocular and binocular presenting near VA will be assessed using LogMAR word reading cards, viewed at habitual working distances in the range of 25–40 cm. Reading fluency will be assessed as the time taken to read a block of text (Pepper Visual Skills for Reading Test cards) 0.3 log units larger than threshold. Following refraction, VAs at distance and near and contrast sensitivity will be assessed through best corrected VA.

For distance uniocular and binocular presenting VA, mild-moderate VI will be categorized as VA > 0.3 and ≤ 1.0 log units, while severe VI will be defined as VA > 1.0 log units. The proportion in each category will be compared between groups.

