### Sample size

Pilot data collected from 31 participants residing in a single-site aged care facility were used to guide power calculations for this study ([name], [name], [name], [name]: Vision Optimisation in Residential Care: A pilot study, unpublished, 2011). They showed that following correction, 30% of participants had improved distance vision by at least two lines and 30% of the participants improved by ≥ 0.2 Log units on a text reading chart for near vision. Therefore, the sample size calculation is based on achieving a 30% improvement in VA (near and distance vision) at two- and six-month follow-up visits in the intervention group compared to controls. The anticipated effect size will be ~ 0.65 based on our pilot work. At a significance level of 0.05, with 38 participants in each arm (overall total of 76 participants) we will have 80% power to detect a group difference. We assume an intra-cluster correlation coefficient (ICC) within-facility of 0.05 which corresponds to the levels found in similar work in nursing homes [28]. The inflation factor (or design effect) will be estimated using the following formula: Inflation factor = 1+ (number of patients per facility [50]-1) X ICC = 3.5. To take cluster design into account, we need a total sample size of 266 [76 × 3.5]. However, to adjust for non-compliance with the intervention (~ 10% due to people who seek vision care on their own in the usual care arm, or people who refuse the intervention in the intervention arm) and loss to follow-up (~ 25% largely due to deaths), the effective sample size needs to be increased by a factor of 1.48 (1/0.90 × 1/0.75) resulting in an initial enrolment requirement of 395 individuals.

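### The supporting categorical comparison of distance acuity uses a seven-line middle band with no favourable direction and leaves the ≤0.3 group unnamed; the main continuous analysis is not affected

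*Protocol article*

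**What the plan says.** All references are to the protocol article.

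- **Outcomes, Distance and near vision (primary).** For distance presenting acuity, "mild-moderate VI will be categorized as VA > 0.3 and ≤ 1.0 log units, while severe VI will be defined as VA > 1.0 log". The article then says how these bands are used: "The proportion in each category will be compared between groups". No category is named for acuity of 0.3 or better.
- **Settings and study participants.** Entry requires "Presenting distance < 6/12 (0.30; Logarithm of the Minimum Angle of Resolution-LogMAR) and/or near vision" of N8 or worse. A resident can therefore qualify on near vision alone, with distance acuity already at 0.3 or better.
- **Statistical analysis.** The primary outcome is analysed as continuous change in near and distance acuity, by analysis of covariance adjusted for baseline. The bands are not mentioned there.
- **Sample size.** The pilot is cited for the finding that "30% of participants had improved distance vision by at least two lines". The calculation itself uses a standardised effect of about 0.65, giving 38 per arm at 80% power. The bands play no part in it.
- **Refractive correction.** The improvement threshold for this pathway is "at least two lines/10 letters on a LogMAR Chart and/or 0.2 Log units for near". This fixes the conversion: one line is 0.1 log units.

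**The concern.** A comparison of acuity categories should move one way when treatment works, and it should account for every participant. This one does neither clearly.

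1. **Direction.** The mild-moderate band lies between two others. Improvement from severe adds to it and recovery to ≤0.3 subtracts from it. A higher, lower or equal proportion in the intervention arm can each accompany benefit.
2. **Denominator.** Recovery to ≤0.3 means no longer meeting the distance entry criterion, yet that state is not among the listed categories. If proportions are taken over the two named bands only, recovered residents leave the denominator and the severe share rises.
3. **Coarseness.** The middle band is wide compared with the two-line gain that the article treats as an improvement.

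At stake is how a supporting result reads: it could be null, or point the wrong way, beside a positive continuous analysis.

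**Working it through.** **Sizing, reproduced first.** Two means, standardised difference 0.65, two-sided 0.05 (sidedness is not stated): 38 per arm gives power 0.81. Then 76 × 3.5 = 266, and 266 / 0.90 / 0.75 = 394, against the stated 395. The sample size thus belongs to a continuous comparison of means.

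**Band width.** 1.0 − 0.3 = 0.7 log units. At 0.1 per line this is seven lines. At 10 letters per 0.2 log (0.02 per letter) the band holds 35 letter steps, 0.32 to 1.00.

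**An exact two-line gain (0.2 log).**
- Baselines 0.32 to 0.50 (10 steps) reach ≤0.3. If baselines are uniform over the band, 10/35 = 28.6% change category and 71.4% do not.
- Baselines 1.02 to 1.20 move from severe to mild-moderate.
- Baselines 0.52 to 1.00 change no category.

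**Direction.** The article gives no baseline distribution, so this one is assumed: uniform from 0.32 to 1.60, which is 65 letter steps, 35 mild-moderate and 30 severe. Let 30% of the intervention arm and no controls gain exactly two lines.

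| Category | Control | Intervention |
|---|---|---|
| ≤0.3 | 0% | 0.30 × 10/65 = 4.6% |
| Mild-moderate | 35/65 = 53.8% | 53.8% + 4.6% − 4.6% = 53.8% |
| Severe | 30/65 = 46.2% | 46.2% − 4.6% = 41.5% |

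At the effective 38 per arm (266 / 3.5 / 2), power for the severe contrast is about 6%. For the unnamed ≤0.3 group it is about 26%. The mild-moderate contrast is exactly null.

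**Sensitivity to the assumed baseline** (same 30% response, 38 per arm, all participants in the denominator):
- Uniform 0.32 to 1.00: mild-moderate 91.5% against 100%, power about 45%.
- Right-skewed towards 0.3: ≤0.3 in 16.0% against 0%, power about 74%; mild-moderate 78.7% against 93.6%, power about 47%.
- All within 0.32 to 0.50: mild-moderate 70% against 100%, power about 97%.
- All within 0.52 to 1.00: no category changes at all.

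Power therefore ranges from nothing to about 97%, depending on a distribution that the article does not give.

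**Denominator.** Assumed: 30 severe and 120 mild-moderate, so severe is 30/150 = 20% of the two named bands. If 40 mild-moderate residents recover and nobody worsens, severe becomes 30/110 = 27%. With everyone kept in the denominator it stays at 30/150 = 20%, and the 40 recoveries are visible.

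**A case where the comparison does respond.** Assumed, 198 per arm: control 30 severe, 120 mild-moderate, 48 at ≤0.3; intervention 15, 120 and 63. The mild-moderate count is unchanged (120 + 15 − 15). Severe falls from 30/198 = 15.2% to 15/198 = 7.6%: pooled proportion 45/396 = 0.114, standard error 0.0319, z = 0.0758 / 0.0319 ≈ 2.4. Dividing by √3.5, for the article's own design effect, gives about 1.3.

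**The case against.** The strongest reply is that the bands are a closing, supporting comparison. Effectiveness is tested by baseline-adjusted analysis of covariance on continuous change, where a move from 0.9 to 0.5 counts for its full 0.4 log. That stands, and it limits the point.

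A reader might infer that the categories cannot register a two-line gain. They can: gains from 0.4 or 0.5 cross 0.3, and gains from 1.1 or 1.2 cross 1.0.

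A reader might also infer that the response rate on which the trial was sized goes untested. The article does say that "the sample size calculation is based on achieving a 30% improvement in VA (near and distance vision"), but the figure entered in the calculation is the standardised effect of about 0.65, which matches the continuous analysis. A responder outcome may be specified in the full protocol or analysis plan, neither of which is shown, and statisticians differ on dichotomising a continuous measure. Its absence from a condensed article is not an error.

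It is also fair to say that each category is compared, not only the middle one; that severe has a clear favourable direction when everyone is counted; and that ≤0.3 is then the implied complement, which also accommodates near-only entrants. This answers the denominator problem only if the denominator is all analysed participants, which the article does not say. It does not give the middle band a direction.

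**Conclusion.** The point holds as a weakness of a supporting comparison. Firm from the text: two bands are named, the middle one is seven lines wide and gains and loses residents under benefit, and ≤0.3 is unnamed although it can be occupied at baseline. The sizes (71% of two-line gains changing no category, power of about 6% for the severe contrast, severe share rising from 20% to 27%) rest on assumed baseline distributions or counts. Other assumptions give a sensitive comparison.

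It would be tempting to conclude that the trial could show no difference when the intervention works. The document does not support that: the main inference rests on the continuous analysis, with about 81% power at an effect size of 0.65 on the article's own figures. The change is worth making because the categorical result will be easy to quote and could mislead.

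**What to change.** Replace the per-band comparison of distance presenting acuity with one ordered three-level outcome: ≤0.3; >0.3 to ≤1.0; >1.0. State that all analysed participants form the denominator, including those who entered on near vision alone. Compare the arms with an ordinal model (for example proportional odds) adjusted for baseline category and allowing for facility clustering, and label the result supportive of the continuous analysis. Show the three proportions by arm and visit for description.

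The cost is small. The data are already collected and participants have no added burden. The price is a proportional-odds assumption, which should be checked, and slightly more analysis work.

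Optionally, report descriptively the proportion improving by at least 0.2 log units, which matches the pilot criterion in Sample size. The point does not depend on it.

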#### Other ocular outcomes (secondary)

Quality of vision will be measured using the 30-item Quality of Vision (QoV) scale [19]. Ten symptoms (e.g. glare, hazy vision, blurred vision, distortion) are rated on 4-point scales for Frequency (never, occasionally, quite often, very often), Severity (not at all, mild, moderate, severe), and Bothersome (not at all, a little, quite, very). The QoV results in three scales of frequency of visual symptoms, severity of symptoms, and how bothered the participant is by the symptoms. Higher mean scores represent greater Frequency, Severity, and Bothersomeness of visual symptoms.

Other aspects of visual function will be assessed (visual fields, color vision, and glare and contrast sensitivity [Pelli-Robson charts]) using instruments suitable for domiciliary assessment in accordance with clinical indications and protocols. Pathology will be graded using standardized grading scales. The integrity of the macular and optic disc will be further assessed by optical coherence tomography.

#### Person-centered outcomes (secondary)

Mobility will be assessed using the Aged Care Funding Instrument (ACFI) [20] module 2 developed by the Department of Health and Ageing. This component of the ACFI relates to the participant’s usual day-to-day assessed care needs with regard to mobility. Mean mobility scores will be compared between groups. ACFI data will be collected regularly by residential care facility staff.

Vision-specific QoL will be measured using the Impact of Vision Impairment for Residential Care (IVI-RC). The IVI-RC is a 28-item questionnaire developed to measure the impact of vision impairment on activity limitation and emotional wellbeing, and has been adapted specifically to the aged care setting by the study team from the original 28-item IVI questionnaire [21, 22].

Depressive symptoms will be determined using the Cornell Scale for Depression in Dementia (CSDD) [23]. This measure was chosen due to its suitability for use with individuals with moderate cognitive functioning. The interviews focus on depressive symptoms and signs occurring during the week before the interview. The final ratings of the CSDD represent the rater’s clinical impression. Each item is rated for severity on a scale of 0–2 (0 = absent, 1 = mild or intermittent, 2 = severe). The item scores are added together. Scores of 0–8, 9–13, 14–18, and 19–38 indicate no or minimal, mild, moderate, and major depressive symptoms [24].

Regarding falls rate, residential care settings have an incident reporting system (which varies from paper based to computerized systems) where any incident including falls will be recorded. Falls data will be retrieved from incident reporting systems in the participating residential care facilities and the proportion of falls will be compared between groups.

Health-related QoL will be assessed using the five-dimension EuroQoL (EQ-5D-3L) [25], a descriptive system that covers five dimensions (Mobility, Self-care, Usual Activities, Pain/Discomfort, and Anxiety/Depression). The EQ-5D-3L raw data can be converted to utilities, which will be used for our economic analyses.

With regard to utilization of visual devices (distance and near vision glasses; low vision aids), at the two- and six-month follow-up visits, participants in the intervention arm who have been prescribed spectacles or low vision aids, will be asked to self-report on how often the device has been used during the week, for how long it was used, and for what tasks.

All QoL outcome measures will be interviewer administered. The IVI-RC and the CSDD will initially undergo Rasch Analysis (a form of Item Response Theory) using Winsteps software (version 3.92.1; Chicago, IL, USA) [26] in order to convert the ordinal questionnaire scores to estimate of interval level measures. Mean Rasch scores for the IVI-RC and CSDD will be compared between groups.

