To date, no study has evaluated the impact of providing comprehensive eye care services to individuals with a broad spectrum of ophthalmic conditions and residing in aged care facilities. Therefore, we will implement a prospective, customized, multicentered, and cluster randomized controlled trial (RCT) to evaluate the clinical, person-centered, and cost-effectiveness of a new model of eye care. We will compare the effectiveness of Residential Ocular Care (ROC) with usual care on improving presenting and best corrected near and distance vision (primary outcome) at the two- and six-month follow-up visits. Secondary outcomes will assess the effectiveness of ROC on improving vision-specific QoL, daily functioning, health-related QoL, depressive symptoms, rate of falls, and eye care utilization, compared to the usual care group at the two- and six-month visits, after baseline, and quantify the cost-effectiveness of ROC at six months after baseline.

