### Retention and withdrawal

We will seek to follow up all participants except those who expressly withdraw from the study. Withdrawal at the participant level will be considered if any of the following occurs: participant is lost to follow-up; withdrawal of consent; or death. All withdrawals will be recorded and the reason will be specified.

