### Statistical analysis

The primary and secondary outcomes will be assessed using an intention-to-treat analysis applied to individual participants and repeated using the per-protocol sample (only participants who complete the clinical trial including the second assessment). To compare the effectiveness of ROC with usual care, presenting and best corrected near and distance VA (primary outcome) at the two- and six-month follow-ups will be analyzed and the differences from baseline VA will be used to investigate changes. The near and distance VA change is expected to be normally distributed and analysis of covariance will be used to compare the difference, adjusting for baseline values. Effect sizes for both groups will be calculated using Cohen’s d coefficient [27]. To determine the effectiveness of ROC on secondary outcomes, a Multivariable General Linear Model will be used to compare differences at two and six months from baseline on the IVI-RC, EQ-5D-3L and CSDD. If the EQ-5D-3L data are skewed, a multivariable quantile regression model will be used. Falls data will be compared across intervention and usual care groups at six months using a negative binomial regression if the data are over-dispersed. Changes in mobility will be analyzed using Mann–Whitney U tests. The difference in utilization of distance and near vision glasses and low vision aids between the treatment groups will be compared using the Chi-squared test and the utilization time will be compared using Student’s t-test or non-parametric test if appropriate. A multi-level model with a random intercept parameter will be utilized to account for within cluster correlations. All analyses will be performed using STATA version 15 (StataCorp. 2017. Stata Statistical Software: Release 15. StataCorp LLC, College Station, TX, USA).

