### Missing data

The differences between the intervention and usual care groups in the proportion and reason of participant withdrawal will be compared using the Chi-squared test. The multiple imputations method using chained equations (MICE) will be used to handle missing data.

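### Falls are called a rate, then compared as a proportion with no denominator, then given a count model used only if the data are over-dispersed; one outcome and one model should be fixed

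*Protocol article*

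**What the plan says.** All references are to the protocol article.

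- **Background (objectives).** The secondary outcomes include "depressive symptoms, rate of falls, and eye care utilization".
- **Person-centered outcomes (secondary).** The falls paragraph opens with a rate: "Regarding falls rate, residential care settings have an incident reporting system". It then says that "the proportion of falls will be compared between groups". It does not say what the proportion is a proportion of.
- **Statistical analysis.** "Falls data will be compared across intervention and usual care groups at six months using a negative binomial regression if the data are over-dispersed". No model is named for data that are not over-dispersed, and no exposure term is mentioned. The section ends with a random intercept to account for clustering.
- **Sample size.** The enrolment figure allows for "loss to follow-up (~ 25% largely due to deaths".
- **Retention and withdrawal.** A participant counts as withdrawn if "participant is lost to follow-up; withdrawal of consent; or death". Withdrawals and their reasons are recorded; dates are not mentioned.
- **Missing data.** "The multiple imputations method using chained equations (MICE) will be used to handle missing data". Nothing there is specific to falls or to follow-up ended by death.

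**The concern.** A rate (falls per unit of time), a proportion (residents who fell, or some other fraction) and a count (falls per resident) are different quantities. They take different models and can give different estimates of the same intervention's effect. An analyst following the outcome section would compare proportions; one following the statistical section would fit a count model. The article does not defer the matter: it fixes both, and they conflict.

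Two further points follow.

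- The negative binomial model is conditional on how the data look, so the standard error, and hence the test, depends on a check made on the same data.
- A rate needs a time denominator and none is given, in a population where the plan itself expects a substantial share to leave, mostly by dying, within six months.

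At stake is the interpretation of one named secondary outcome.

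**Working it through.** **1. The definitions side by side.**

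| Section | Quantity named | Denominator | Method |
|---|---|---|---|
| Background | rate | none given | none given |
| Person-centered outcomes, opening | rate | none given | none given |
| Person-centered outcomes, comparison | proportion | none given | none given |
| Statistical analysis | falls data; a count is implied by the model | none given | negative binomial, if over-dispersed |

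The third and fourth rows cannot both be executed for a single outcome. The time points also differ: the Abstract and Background list secondary outcomes at two and six months, while the falls analysis is at six months only.

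**2. The plan's own figure.** No falls figure is stated. The 25% loss belongs to the enrolment calculation for the primary outcome, which reproduces: 76 × 3.5 = 266, and 266 / (0.90 × 0.75) = 394.1, against 395 stated. The 25% is a planning assumption, not observed loss, and is not split by arm.

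**3. Does rate versus proportion matter?** The article gives no fall rate or dispersion, so I assume a mean μ of 0.5 to 1.5 falls per resident per six months and a dispersion k of 0.5 to 2. Under a negative binomial, P(at least one fall) = 1 − (1 + kμ)^(−1/k). Take a true rate ratio of 0.70:

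- μ = 0.5, k = 0.5: 0.276 / 0.360, a ratio of 0.77.
- μ = 1.0, k = 1: 0.412 / 0.500, a ratio of 0.82.
- μ = 1.5, k = 2: 0.432 / 0.500, a ratio of 0.86.

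The same effect reads as 0.70 on one scale and 0.77 to 0.86 on the other.

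**4. Does the conditional model matter?** Suppose the check missed over-dispersion and a plain Poisson model were used (my assumption, since the article names no alternative). The size of a nominal 5% Wald test is 2 × [1 − Φ(1.96 / √(1 + kμ))]:

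- μ = 0.5, k = 0.5: 1.96 / √1.25 = 1.753, size 8%.
- μ = 1.5, k = 2: 1.96 / √4 = 0.98, size 33%.

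This is the size given that the check has failed, and it ignores clustering. It is not the size of the whole two-step procedure.

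**5. Does the missing time denominator matter?** With constant exit hazard and six-month retention S, the mean observed share of six months is (1 − S) / (−ln S):

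- S = 0.75: 0.25 / 0.2877 = 0.869.
- S = 0.80: 0.20 / 0.2231 = 0.896.
- S = 0.70: 0.30 / 0.3567 = 0.841.

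With S = 0.75 in both arms, counts fall by about 13% in each and the ratio stays at 1.00. With 80% versus 70% and no true effect, the count ratio is 0.896 / 0.841 = 1.066, and the arm that loses more residents appears to fall less.

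The order of size depends on when exits occur. For 20% versus 30% exits spread evenly, the ratio is (1 − 0.10) / (1 − 0.15) = 1.059; if all exits were at the start, 0.80 / 0.70 = 1.143. A log-time offset returns 1.00 in these cases, provided that the fall rate is constant over time and exit is unrelated to it.

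**The case against.** The strongest reply is that this is a condensed article, that an unseen analysis plan may exist, and that an offset is ordinary content for such a plan. That stands for the offset taken alone: its absence would not be a finding by itself. It does not remove the conflict between the proportion and the count model, which is in the printed text, nor the conditional choice of model, which the article fixes.

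Three stronger readings are tempting and are not supported.

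- **That a resident who dies early is counted as if followed for six months.** No section says so. The analyses are repeated among completers and multiple imputation is planned. Neither settles time at risk, but unadjusted partial counts would be an inference.
- **That the choice among rate, proportion and count would be made after seeing the data.** Only the dispersion step is data-dependent in the text. A Poisson alternative would target the same rate ratio and change only the standard error.
- **That the plan's 25% loss biases the comparison.** The article gives no difference between arms, and equal loss with equal timing gives no bias. It also plans to compare withdrawal between arms, so a difference would be seen, though not corrected.

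It is also fair to say that falls come from facility incident systems. A resident who misses a study visit but stays in the facility still has falls recorded, so the time-at-risk argument applies to deaths and departures, not to all loss to follow-up.

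**Conclusion.** The concern holds as an inconsistency in how the falls outcome is defined, joined to a model choice that depends on the data and a rate with no time denominator. The contradiction needs no assumptions; it can be read from the three sections.

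The sizes are illustrative. The gap between a rate ratio of 0.70 and a proportion ratio of 0.77 to 0.86 rests on assumed fall rates and dispersion. The shift of about 7% rests on an assumed 80% versus 70% retention with constant hazard and no true effect, and vanishes when loss and timing are equal. The article does not support a claim that bias will occur.

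This should be corrected because the change is cheap and the plan itself expects deaths to cut follow-up short. The importance is moderate: falls is one of several secondary outcomes.

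**What to change.** Use one definition in the Background, Person-centered outcomes and Statistical analysis sections: falls per person-time at risk, from baseline to six months.

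- Analyse it by negative binomial regression regardless of any dispersion check.
- Keep the facility random intercept, which is already planned, and add the log of time observed in the facility as offset.
- Report the proportion of residents with at least one fall as descriptive, with residents as the stated denominator.
- State in the Missing data section that the multiple imputation does not extend to falls after death.

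The cost is wording plus exit dates. The sponsor should confirm that dates of death or departure are held, because the Retention and withdrawal section mentions only the withdrawal and its reason. If they are not held, they would have to be obtained, for example from the facilities. No change to enrolment or to the primary analysis is needed.
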